#### NMP, hepatic steatosis and pre-clinical animal studies

Steatotic livers constitute the largest individual cohort of organs which might be salvaged through active intervention during NMP [22, 23, 25, 26, 27, 28, 29]. Pre-clinical models demonstrate that ex-situ liver function can be enhanced and IHTG content reduced using NMP [22, 23].

Jamieson et al. [23] investigated the effect of NMP alone on steatotic porcine livers during 48-h perfusions. Steatotic porcine livers maintained perfusate base excess, factor V and bile production during NMP and demonstrated comparable haemodynamics and markers of liver injury to lean controls. MaS was reduced from 28 to 15% with reduction in lipid droplet size by the end of preservation [23]. This study demonstrated mobilisation of fat from the liver into the perfusate. Indeed, one limitation of the study was the recirculation of secreted TGs in the circuit, thereby making the perfusate extremely lipaemic. It was thought that this might be a factor that limited the amount of fat that could be extracted by perfusion alone.

Nagrath et al. [22] used an experimental oxygenated normothermic model to investigate the effect of a ‘defatting cocktail’ on steatotic livers from Zucker rats over 3-h perfusions. The ‘defatting cocktail’ combined six pharmacological agents (see Table 2). IHTG content was reduced by 65% with increased hepatic lipid metabolism. Notably, a 30% reduction in IHTG content was seen in the control group with no defatting agents.

**Table 2 Tab2:** Defatting agents used in Nagrath et al [22]

Defatting agent	Function
PPARδ ligand GW501516	Increase fatty acid β-oxidation
Peroxisome proliferator-activated receptor (PPAR) α ligand GW7647	Increase mitochondrial fatty acid oxidation
Cyclic adenosine monophosphate (cAMP) activator forskolin	A glucagon mimetic cAMP activator, increases lipolysis and fatty acid oxidation
Pregnane X receptor ligand hypericin	Increase β-oxidation (very long chain fatty acids)
Visfatin	An insulin-memetic adipokine, role not fully understood
Scorparone	An androstane receptor ligand, upregulates PPAR

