#### NMP, hepatic steatosis and discarded human livers

Liu et al*.* [24] perfused ten discarded livers with variable degrees of baseline steatosis for 24 h and demonstrated a significant increase in perfusate TG levels over the duration of the perfusion, suggesting mobilisation of IHTG. However, no histological reduction in IHTG content was observed. Banan et al. reported results from two human livers which were preserved normothermically with two defatting agents (L-carnitine and exendin-4); one of these showed a 10% reduction in the degree of MaS after 8 h NMP [25].

When our group explored the effect of NMP (alone) on transplanted steatotic human livers (as part of a larger trial), we observed clear differences in TG metabolism during preservation compared to lean livers. As with previous groups [24, 25, 27], we observed significant increases in perfusate TG and 3-hydroxybutyrate (3-OHB) (a marker of hepatic fatty acid oxidation) during perfusion (Fig. 1) [29]. This suggests that a steatotic liver upregulates pathways to dispose of intrahepatic fatty acids, including mobilising and secreting more very low-density lipoprotein (VLDL)-TG and increasing ketone body production (Fig. 2). Despite these changes in TG metabolism, the amount of IHTG did not change when assessed histologically. Furthermore, although steatotic NMP livers demonstrated significantly superior post-transplant biochemical function compared to steatotic cold-stored livers (implying less preservation injury), there was still evidence of greater injury than in lean counterparts, with a significantly higher post-operative peak serum aspartate aminotransferase (AST) level (*p* = 0.02) [29].

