#### Mechanistic studies outcome measures

The identification of novel markers could augment current practice by predicting the outcome of each liver with objectivity. The mechanistic studies will test hypotheses based on previous published studies that have investigated markers in the field of NMP and will inform development of functional criteria and optimisation of future defatting protocols:To measure the effect of the intervention on the histological degree of steatosis:Histological quantification of MaS measured pre-perfusion, post-perfusion and during re-perfusion in the recipient. We hypothesise that the intervention of defatting will reduce the degree of MaS and severity of NAFLD activity score [75].To measure the effect of the intervention on markers on of hepatic lipid metabolism:Perfusate TG, insulin, ketone bodies and cytokines associated with IRI will be measured at baseline (pre-NMP) and during preservation (1, 2, 4 and 6 h and end of perfusion). Further measurements taken from the recipient peri-operatively (before transplant) and re-perfusion (following liver transplantation). This will provide insight into changes in intrahepatic lipid handling and inflammation. We hypothesise that the intervention of defatting will ‘repartition’ intrahepatic fatty acids away from esterification into oxidation pathways leading to a decrease in IHTG and a decrease in IRI-associated cytokine production [70].Perfusate FGF-21 will be measured at baseline (pre-NMP) and during preservation (1, 2, 4 and 6 h and end of perfusion). Further measurements taken from the recipient peri-operatively (before transplant) and re-perfusion (following liver transplantation). FGF-21 is a hormone produced in the liver involved in energy homeostasis; its secretion is attributed to metabolic stress. There is evidence that serum FGF-21 is a useful marker for steatosis and correlates with increasing steatosis grade [76]. We hypothesise that the defatting intervention will reduce FGF-21.To understand the structural, cellular and metabolic effects of defatting on steatotic livers.Genomic analysis of samples taken pre-perfusion, post-perfusion and following re-perfusion in the recipient:◦Transcriptomics: a complex signalling cascade regulates metabolic processes within the liver. To understand the effect of NMP and the defatting intervention, genomic analysis of liver tissue will be undertaken. We hypothesise that the defatting intervention will lead to downregulation in pathways related to fat synthesis and inflammation and an upregulation in pathways related to fat disposal. Samples from livers will undergo RNA sequencing of the liver and this will be correlated with clinical outcomes. Changes in gene expression will be mapped with changes occurring in biological pathways, inferring biological changes during NMP.Proteomic and glycomic analysis of perfusate samples taken at baseline (pre-NMP) and during preservation. Further measurements taken from the recipient peri-operatively (before transplant) and re-perfusion (following liver transplantation):◦Proteomics: a recent study investigating the use of NMP to increase utilisation of high-risk donor livers, identified protein clusters that were able to discriminate between transplantable and non-transplantable livers (22 out of 31) as well as markers predictive of post-transplant complications [77]. We aim to determine the effect of the intervention on protein expression associated with hepatic steatosis, inflammation and IRI.◦Glycomics: the liver perfusate glycome profile may form part of future functional criteria [78]. A recent study found that the abundance of a single glycan, agalacto core-alpha-1,6-fucosylated biantennary glycan (NGA2F) was significantly higher in the perfusate of livers that developed PNF. We will test this hypothesis in sequential perfusate samples.

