An ITT analysis will be performed for the primary outcome and secondary (donor liver related) outcomes. Secondary (recipient) outcomes will be analysed using a mITT approach. This analysis will exclude livers perfused but not transplanted for any reason.

For the mechanistic work, measures will be compared before and after perfusion to assess for a change during machine perfusion. A paired *t*-test will be used to compare the means of these levels pre- and post treatment to determine whether any change is statistically significant. For all analyses with statistical testing, a *p*-value of < 0.05 will be used to determine statistical significance.

Full details of the statistical analysis plan will be made available on the ISRCTN registry webpage (ISRCTN 14957538: 10.1186/ISRCTN14957538).

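### The only test stated for the mechanistic work, a paired before/after t-test, estimates change during perfusion and not the effect of defatting

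*Protocol article*

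**What the plan says.** The section on mechanistic studies outcome measures states its aims in terms of the intervention. The first is "To measure the effect of the intervention on the histological degree of steatosis", with the directional hypothesis "We hypothesise that the intervention of defatting will reduce the degree of MaS". The second concerns the effect of the intervention on markers of hepatic lipid metabolism, including perfusate triglyceride, ketone bodies and cytokines. FGF-21 is expected to fall with defatting.

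The description of statistical methods gives the mechanistic work its own paragraph: "For the mechanistic work, measures will be compared before and after perfusion to assess for a change during machine perfusion". The test follows: "A paired *t*-test will be used to compare the means of these levels pre- and post treatment". For every analysis with testing, "a *p*-value of < 0.05 will be used to determine statistical significance". No comparison between the randomised arms is mentioned for these measures. The linear, logistic and Cox regressions in the same section are stated for the primary and secondary endpoints, and the mechanistic outcomes are listed separately from those.

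**The concern.** The aim is a contrast between arms and the stated test is a contrast within livers over time. Every liver in the trial is perfused, so a before/after change contains whatever NMP, elapsed time and sampling variation contribute, plus any contribution from defatting. The paired test cannot separate these.

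The protocol's own background shows that this matters. In the rat study of the defatting cocktail, "Notably, a 30% reduction in IHTG content was seen in the control group with no defatting agents". In pigs on NMP alone, macrovesicular steatosis fell from 28% to 15%. In the group's own steatotic human livers on NMP alone, perfusate triglyceride and 3-hydroxybutyrate rose significantly, and the authors comment: "This suggests that a steatotic liver upregulates pathways to dispose of intrahepatic fatty acids". These are the same kinds of marker that the trial will use to show a defatting mechanism.

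At stake is the mechanistic conclusion. A significant change on the machine could be taken as evidence of defatting when the control arm changed just as much. The randomised control arm, which would answer the question directly, has no stated role in this part of the analysis.

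**Working it through.** **Plan's own figure.** None is given for the mechanistic measures. The only design figure is power above 80% for the primary endpoint (30 per arm, 65% against 95%). It reproduces at 84.6% with the pooled two-sided formula and has no bearing on this point.

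**Inputs.** From the protocol: 60 livers, 1:1, 30 per arm, significance at p < 0.05. Assumed: two-sided testing; normally distributed changes; all 30 livers per arm measured; and a common change of 0.3 or 0.5 SD, in units of the SD of the change, because the protocol gives no SD for any mechanistic measure.

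**What each analysis estimates.** Let the mean change be *m* in the control arm and *m* + *e* in the defatting arm, where *e* is the intervention effect.
- Paired test in the defatting arm: *m* + *e*.
- Paired test pooled over equal arms: *m* + *e*/2.
- Between-arm comparison: (*m* + *e*) − *m* = *e*.

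Only the last is the stated aim.

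**Rejection rate of the paired test when *e* = 0.** The statistic follows a noncentral t distribution with noncentrality *m*√n (*m* in SD units) and n − 1 degrees of freedom. Two-sided critical values are 2.045 for n = 30 and 2.001 for n = 60.

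| Common change | Livers in test | *m*√n | Significant |
|---|---|---|---|
| 0.3 SD | 30 | 0.3 × √30 = 1.64 | 36% |
| 0.3 SD | 60 | 0.3 × √60 = 2.32 | 63% |
| 0.5 SD | 30 | 0.5 × √30 = 2.74 | 75% |
| 0.5 SD | 60 | 0.5 × √60 = 3.87 | 97% |

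A simulation of 40,000 trials agrees (36%, 63%, 76%, 97%). In the same trials a two-sample t-test on change between arms is significant in about 5% at each value.

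**Testing each arm and comparing verdicts.** Calling it an effect when one arm is significant and the other is not does not help. With *e* = 0, exactly one arm is significant in 30% of simulated trials at 0.2 SD, 46% at 0.3 SD, about 50% at 0.36 SD and 37% at 0.5 SD. About half of these favour defatting.

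**Pooling can also hide an effect.** If a marker rises by 0.5 SD in one arm and falls by 0.5 SD in the other, the pooled mean change is (0.5 − 0.5)/2 = 0 although the arms differ by 1 SD. Perfusate triglyceride is a candidate: it rose under NMP alone, and the apheresis filter lowered circulating levels in the preliminary study.

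**What the between-arm test can detect.** With 30 measured livers per arm, 80% power needs a difference in change of (1.96 + 0.84) × √(2/30) ≈ 0.72 SD. With 25 per arm it is 0.79 SD and with 20 it is 0.89 SD. Adjustment for baseline would usually improve on this.

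**The case against.** Several counter-arguments have force.

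- The test is labelled accurately, as assessing change during perfusion, and the protocol never says that a significant change will be credited to defatting. The transcriptomic aim also covers NMP itself. This stands: the paired test answers a legitimate question, and the percentages above become error rates only if change is read as an intervention effect. It does not answer the aims and hypotheses that are worded as effects of defatting.
- The SAP is deferred to the registry. A reader might infer that no between-arm mechanistic comparison is planned. The document supports only that none is stated here.
- The human evidence for histology points the other way. The protocol reports no histological change in liver fat on NMP alone, both in its own transplanted steatotic livers and in a 24-hour series of ten discarded livers. The concern is therefore best documented for perfusate markers. For histological steatosis it rests on the animal data and on the logic of the design.
- A reader might infer that the 0.05 threshold will be applied gene by gene to the RNA sequencing and produce a flood of false positives. The text does not say so. It describes pathway mapping and correlation with outcomes, and it gives no number of genes. Multiplicity handling for such data is commonly left to the SAP.
- Thirty per arm is a ceiling for tissue measures, because pre-implantation research biopsies need donor-family consent to research.

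**Conclusion.** The point holds in this limited form: the one method stated for the mechanistic work does not estimate the quantity named in its aims. This is a mismatch between stated aim and stated method, not a detail left out. It follows from the structure of the test and does not depend on the assumed numbers. The size does: for an equal change of 0.3 to 0.5 SD in both arms, about 36% to 75% significant with 30 treated livers and 63% to 97% with all 60, against about 5% for the between-arm test. The text does not say whether the paired test is run per arm or pooled; neither gives the effect of defatting.

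A reader might infer that the trial's main conclusions are at risk. They are not. The primary and secondary endpoints have their own between-arm models, and the mechanistic studies are analysed after the main clinical outcomes. The correction is worth making before the mechanistic data are analysed, but it is not critical to the trial.

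**What to change.** State as the main mechanistic analysis a between-arm linear regression (ANCOVA): post value on randomised arm, pre-perfusion value and donor type (DBD/DCD), reported as an adjusted difference with 95% confidence interval. Use the 6 h sample as the post value for perfusate markers. For tissue use the end-of-perfusion biopsy, since no 6 h biopsy is scheduled. Do not adjust for perfusion duration: it may run from 6 to 24 h, is determined after randomisation and could be affected by treatment, so adjusting for it could bias the comparison. Keep paired within-arm changes as description only, without using their p-values as evidence of defatting.

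Check the SAP first. If it already contains a between-arm comparison, only the protocol wording needs aligning. Otherwise the cost is a wording change and slightly more analysis. The samples named here are already in the collection schedule.

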## Objectives {7}

The experimental data outlined above suggest that the combination of NMP and defatting may be effective in reducing the fat content of livers and improving perfusion parameters to meet functional criteria for transplantation. In this first clinical study, the primary objective is to confirm the safety and assess efficacy of the NMP-defatting protocol in steatotic donor livers intended for transplant. The secondary objective is to test the feasibility of the (i) inclusion criteria (false positives and negatives); (ii) delivery of intervention and (iii) the study endpoints. These objectives will provide information of likely effect sizes in order to design a subsequent phase III study in the future.

The mechanistic studies will be analysed subsequent to the main clinical outcomes. These will be carried out for two broad reasons (i) to identify more sensitive and specific markers of transplantability and (ii) to understand the process of defatting that leads to a steatotic organ being reconditioned. The proposed mechanistic studies and associated outcome measures are described in the outcome section of this protocol.

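### One p < 0.05 threshold is set for all tests, including the RNA-sequencing, proteomic and glycomic work, with no false-discovery control named for those platforms

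*Protocol article*

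**What the plan says.** The rule stands in the protocol article under Description of statistical methods. Its scope is given first: "For the mechanistic work, measures will be compared before and after perfusion to assess for a change during machine perfusion". The method follows: "A paired *t*-test will be used to compare the means of these levels pre- and post treatment". No mechanistic measure is excepted. The next sentence sets the threshold: "For all analyses with statistical testing, a *p*-value of < 0.05 will be used to determine statistical significance".

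Mechanistic studies outcome measures shows what that work contains. Beside scalar measures such as macrovesicular steatosis, perfusate triglyceride and FGF-21, it lists three omics platforms. For transcriptomics: "Samples from livers will undergo RNA sequencing of the liver and this will be correlated with clinical outcomes". For the perfusate: "Proteomic and glycomic analysis of perfusate samples taken at baseline (pre-NMP) and during preservation". Under glycomics it cites one glycan, NGA2F, and adds: "We will test this hypothesis in sequential perfusate samples".

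The results have a use. Objectives {7} gives as one reason for the mechanistic studies "to identify more sensitive and specific markers of transplantability". The outcome section says that they "will inform development of functional criteria and optimisation of future defatting protocols".

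For the secondary endpoints, the same statistical section promises little testing and puts the weight on effect sizes with 95% confidence intervals. It does not extend that restraint to the mechanistic work. Full analysis details are referred to a SAP on the trial registry page, which is not shown here.

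**The concern.** A fixed 5% threshold suits one test of one hypothesis. On a platform that measures many features at once, the same threshold applied to each feature flags about 5% of those that do not change at all. Had the article said nothing about significance in the mechanistic work, leaving the matter to the SAP would be unremarkable. It does speak, however. It sets one threshold for every test, directly after fixing the mechanistic test, and makes no exception for high-dimensional data. A SAP with false-discovery control would have to qualify that sentence.

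What is at stake is the list of candidate markers. If chance findings make up much of that list, they can be taken up when functional criteria and later defatting protocols are developed.

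**Working it through.** **1. The plan's own figure.** The article states no error rate for the mechanistic tests. Its only checkable figure nearby is the primary-endpoint power (Sample size {14}): 30 livers per arm, 65% against 95%, 5% significance (taken as two-sided), power above 80%. With pooled variance, z = [0.30 × √30 − 1.96 × √(2 × 0.80 × 0.20)] / √(0.65 × 0.35 + 0.95 × 0.05) = (1.643 − 1.109) / 0.524 = 1.02, so power is 84.6%. The figure reproduces. The primary analysis is a single 5% test, and nothing below changes its error rate.

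**2. Expected false positives per contrast.** With m truly unchanged features, each tested at 0.05, the expected number of false positives is 0.05 × m. Correlation between features alters the spread of this count but not its mean. The article gives no m, so the values are assumptions.

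| Assumed unchanged features | Expected false positives |
|---|---|
| 50 | 2.5 |
| 100 | 5 |
| 1,000 | 50 |
| 5,000 | 250 |
| 10,000 | 500 |
| 20,000 | 1,000 |

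Each further contrast, such as another sampling time or the correlation with clinical outcomes, brings its own count.

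**3. Share of flagged features that are false.** If a fraction π of features truly changes and each such change is detected with power w, the false share is about (1 − π) × 0.05 / [(1 − π) × 0.05 + π × w]. For π = 0.05 and w = 0.80 this is 0.0475 / (0.0475 + 0.04) = 54%. Both inputs are assumptions.

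| Truly changing | w = 0.80 | w = 0.50 |
|---|---|---|
| 1% | 86% | 91% |
| 5% | 54% | 66% |
| 10% | 36% | 47% |
| 20% | 20% | 29% |
| 50% | 6% | 9% |

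The problem is severe if few features change and mild if half of them do.

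**4. Where the rule does little harm.** The ten cytokines named among the histological and biochemical secondary outcomes would give 10 × 0.05 = 0.5 expected false positives if all were null. The chance of at least one is 1 − 0.95^10 = 40% if they are independent, and about 29% at a correlation of 0.5 (simulated). The NGA2F hypothesis concerns one named feature, for which a 5% level is ordinary.

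**The case against.** The strongest reply is that the article never says the p-values are unadjusted. A 0.05 cut-off can be applied to adjusted p-values, and multiplicity within an omics platform is often left to a SAP. A reader might infer that the plan commits itself to raw per-gene testing. The text does not go that far: its paired test speaks of mean levels, which suits scalar measures, and its transcriptomic text speaks of mapping expression changes to biological pathways. This stands, and it limits the point to what the rule permits as written.

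A reader might also infer that the programme is bound to return many false markers. That depends on feature counts and on the share of true nulls, and the article gives neither. It does not fit the cytokines or the single glycan.

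A third tempting step is to count 16 scalar measures: steatosis, NAFLD activity score, triglyceride, insulin, ketones, FGF-21 and ten cytokines. The family-wise error would then be 37% at a correlation of 0.5 (56% if independent, 15% at 0.9). That family is assembled. The ten cytokine names come from a secondary outcome in recipient blood, while the mechanistic section refers only to cytokines associated with reperfusion injury. The rates also require every null to be true, although the article's background already reports rises in perfusate triglyceride and 3-hydroxybutyrate during perfusion.

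Finally, no rule in the article carries a marker with p < 0.05 into a later trial, and the effect sizes for the phase III design are tied to the primary and secondary objectives. That is also correct. It does not answer the narrower point: the threshold sentence covers the omics work, is universal, and names no safeguard.

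**Conclusion.** The concern holds for the omics platforms. The article fixes one threshold for all testing, includes RNA sequencing, proteomics and glycomics in the work it has just described, uses that work to look for markers, and names neither multiplicity control nor an exploratory label. Applied per feature, the rule gives about 50 expected false positives per 1,000 truly null features per contrast, or 250 to 1,000 for an assumed 5,000 to 20,000 null genes. These sizes rest on per-feature testing of unadjusted p-values and on assumed counts.

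The primary endpoint is not affected, and the documents do not support a claim about the trial's error rate as a whole. For the scalar mechanistic measures, a formal hierarchy is a matter of judgement; presenting them as exploratory is enough. The sentence should be corrected, but the point does not threaten the trial's main conclusion.

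**What to change.** Reword the threshold sentence under Description of statistical methods:

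- Limit p < 0.05 to the primary endpoint and to single hypotheses named in advance, such as the NGA2F glycan.
- For transcriptomics, proteomics and any untargeted glycomics, declare findings by the Benjamini-Hochberg false-discovery rate, for example at 5%, within each platform and each contrast.
- Report the scalar mechanistic measures as estimates with 95% confidence intervals, labelled exploratory, in line with the approach already taken for the secondary endpoints.

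If the SAP already controls false discovery, no new method is needed; the article's sentence should be brought into line with it.

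The cost is one or two sentences and a routine adjustment in the omics code. The downside is fewer nominally significant mechanistic results, and some real but weak signals will not be declared.
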